### Blending of analysis across designs

For the primary outcome, results will be combined across individually and cluster-randomized designs using a marginal proportional hazards model. We will assume that these different designs represent independent sources of evidence. Compared to the mixed-effects modelling approaches, the marginal model offers a simple marginal interpretation of intervention effects and avoids the need to specify the correlation structure among the observations. Stratified marginal models will be considered to allow differential baseline hazard functions across studies. The marginal model will be fitted under a ‘working independence’ assumption and inference will be performed using the robust sandwich variance estimator which ensures valid inference when there is a within-cluster dependence in event times.^
19
^ Alternative randomization-based inference methods could also be used^
20
^ that can account for design features (e.g. stratified randomization) in a straightforward way through restricted permutation. Another commonly used approach to combine estimates from different studies is through the use of meta-analysis approaches. When analysing censored data with a Cox proportional hazards model, the inverse-variance estimator based on the fixed-effects meta-analysis method is asymptotically equivalent to the maximum partial likelihood estimator using pooled individual-level data under a stratified model which assumes a different baseline hazard function across studies.^
21
^

It is important to note that the estimand for VE under individual randomization is in general different from the one under cluster randomization, with the former targeting direct vaccine effectiveness and the latter total vaccine effectiveness.^
22
^ (Although when direct effectiveness is high or clustering low, i.e. ICC is near zero, the two are nearly identical.) Without differentiating the two, the parameter represents a weighted average. One could parameterize the total effect as the sum of direct effects and indirect effects in the model. The availability of data from both individual and cluster-randomized trials permits the estimation of both by including an interaction term between the treatment variable and an indicator variable that takes value 1 if data are from the cluster-randomized trials and 0 otherwise.

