### Study sample size for individually randomized designs

The trial is endpoint-driven, as the primary analysis for each vaccine arm versus the concurrent shared placebo/control arm is triggered by occurrence of a total of 150 cases of MARV disease across these two arms. The primary analysis results will be reported but blinded follow-up will still continue. We assume a 1% cumulative attack rate in the control arm over 6 months of outbreak time. The trial period could involve several years of follow-up and across outbreaks. As stated above, there will be two interim analyses at the points when 1/3 and 2/3 of events have occurred, respectively. We use the O'Brien-Fleming-type spending function for both false-positive and false-negative errors. All the sample size calculations were conducted using the R package *rpact*.

For example, with a target level VE of 60%, with 150 total endpoints in a pairwise comparison, there is approximately 90% power to reject VE less than or equal to 30% if true VE is 60%, based on a logrank test with one-sided type I error rate of 0.025. With equal allocation to the active vaccine arm and the control arm, a minimum follow-up of 3 months for the last accrued participant and an annual drop rate of 10%, we calculated sample sizes for different accrual rates (Table 1). If on average 30,000 participants will be accrued each month, we need 18,062 participants per arm and an expected study duration of 9.1 months. Lower accrual rates are associated with longer study durations but smaller sample sizes. Using the sample size of 18,062 per arm, we simulated 100 times exponentially distributed event times without early stopping to investigate the coverage of the two-sided confidence interval of the VE estimate. The average total number of events is 179 and the average 95% confidence interval for the VE is (45%, 71%). The lower confidence bound would exclude 30% with a probability of 0.93, and the point VE estimate is greater than 50% with a probability of 0.91. We performed a sensitivity analysis, varying the accrual rate, assuming a 1% cumulative attack rate in the control arm over a 12-month period with an annual dropout rate of 10%, and a minimum follow-up of 6 months after the last accrual (Table 1). The sample size increases with increasing accrual rate to about 18,062 participants per arm. The best sample size is about 20,000 participants per arm, or about 40,000 participants per vaccine/comparator combination.

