### Study sample size for a mixture of individually and cluster-randomized designs

For those designs involving cluster randomization, the number of events needed to assess efficacy and sample sizes would be increased to account for the correlation within clusters. While the intraclass correlation coefficient (ICC) parameter for continuous and binary outcomes is commonly used, it is not easily extended to time-to-event outcome settings because of the presence of censoring (e.g. losses-to-follow-up, end-of-study administrative censoring).^
15
^ It has been shown that ICC estimators based on censoring indicators or observed event times can be negatively biased.^16,17^

One way to account for the clustering effect is using an ICC based on the binary event indicator and to inflate the events required by the usual design effect that equals 1 + (*m −* 1) ICC, where *m* is the average cluster size.^
18
^ For the Ebola ring vaccination trial in Guinea, the average ring size was about 80, and the ICC was about 0.05, resulting in a design effect of about 4. Thus, 600 total events would be needed for the design above, resulting in 150 effective events. For mixtures of individually and cluster-randomized designs, the target number of events will be the total number of effective events.

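### In a mixture trial, 150 additive effective events carry less than 150 events of information under the working-independence pooled model

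*Protocol article*

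**What the plan says.** The Protocol article gives its power in the section on sample size for individually randomized designs: "there is approximately 90% power" to rule out a vaccine efficacy (VE) of 30% or less when true VE is 60%, "with 150 total endpoints in a pairwise comparison", "based on a logrank test with one-sided type I error rate of 0.025".

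The next section, on mixtures of individually and cluster-randomized designs, divides cluster events by a design effect. Its Ebola ring example (average ring size about 80, ICC about 0.05, design effect about 4) turns 600 events into 150 effective events. For a mixture, "the target number of events will be the total number of effective events".

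Under Blending of analysis across designs, "results will be combined across individually and cluster-randomized designs using a marginal proportional hazards model". The model is fitted under working independence with a robust sandwich variance, and stratified versions are to be considered. Meta-analysis is named as another common approach, with the remark, made for stratified pooling, that "the inverse-variance estimator based on the fixed-effects meta-analysis method is asymptotically equivalent to the maximum partial likelihood estimator using pooled individual-level data".

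**The concern.** The event trigger and the primary analysis weight cluster events differently. The trigger counts a cluster event as 1/DE of an individually randomised event. The analysis counts it as one whole event when it forms the estimate. An additive count of effective events equals the information only if each design's log hazard ratio is weighted by its own inverse variance, and working independence does not do that.

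At stake are the power of the mixture at its stated target and the timing of the interim looks at 50 and 100 events. Blending is meant to speed up the evidence, yet adding cluster events can make the estimate less precise.

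**Working it through.** **Inputs from the article.** One-sided alpha 0.025; null hazard ratio 0.70; alternative 0.40; 1:1 allocation; 150 events; DE about 4. The formula 1 + (m − 1) × ICC with m = 80 and ICC = 0.05 gives 1 + 79 × 0.05 = 4.95, so 4.95 is carried as a second case.

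**Assumption.** The share f of effective events that comes from cluster-randomized parts is not stated, so it is varied from 0 to 1.

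**Step 1: reproduce the 90%.** The effect to detect is ln(0.70/0.40) = 0.560. With 150 events:
- The standard error under the null is √(1.70²/(0.70 × 150)) = 0.166.
- The standard error under the alternative is √(1.40²/(0.40 × 150)) = 0.181.
- Power is Φ((0.560 − 1.96 × 0.166)/0.181) = 90.3%.

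The simpler variance of 4/d gives 92.9%. The stated figure of about 90% is therefore reproduced for 150 independent events.

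**Step 2: information under equal weights.** The pooled log hazard ratio weights the designs by raw events. Its variance is 4(E_ind + DE × E_clus)/(E_ind + E_clus)². In units of independent events, the information is

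I = (E_ind + E_clus)²/(E_ind + DE × E_clus).

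Inverse-variance weights would give E_ind + E_clus/DE, which is what the trigger counts. I is smaller than this whenever both designs contribute and DE exceeds 1.

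**Step 3: stop at E_ind + E_clus/DE = 150, with DE = 4.** Power uses the first convention of Step 1, with the 4/d convention in brackets.

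| f | E_ind | E_clus | I | Power |
|---|---|---|---|---|
| 0% | 150 | 0 | 150 | 90% (93%) |
| 5% | 142.5 | 30 | 172.5²/262.5 = 113 | 81% (85%) |
| 20% | 120 | 120 | 240²/600 = 96 | 75% (78%) |
| 50% | 75 | 300 | 375²/1,275 = 110 | 80% (84%) |
| 75% | 37.5 | 450 | 487.5²/1,837.5 = 129 | 86% (89%) |
| 100% | 0 | 600 | 150 | 90% (93%) |

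The minimum is 150 × 4DE/(1 + DE)², reached at f = 1/(1 + DE). For DE = 4 it is 96. For DE = 4.95 it is 150 × 19.8/5.95² = 84, at f = 17%, with power of about 70% (73%). At DE = 4.95, f of 25%, 50% and 75% give 86, 104 and 126.

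**Step 4: simulation check.** Beta-binomial rings of 80 with DE = 4, and attack rates of 1% and 0.4%, gave pooled information of about 97, 109 and 133 at f = 20%, 50% and 75%. Inverse-variance weighting of the same data gave about 144 to 150.

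**Step 5: when blending loses precision.** I is below E_ind alone when E_clus < (DE − 2) × E_ind. At DE = 4, adding 50 cluster events to 100 individual events moves the information from 100 to 150²/300 = 75, while the trigger reads 112.5.

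**Step 6: the looks.** Suppose the first 100 effective events are all individual and the last 50 come from 200 cluster events at DE = 4. Information is 100 at the second look and 300²/900 = 100 at the final one. The fraction at the second look is then 1, not 2/3. At a constant mix the ratios between looks hold, and only the absolute information falls short.

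**The case against.** The case for leaving the text alone has several parts.

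- **The trigger is partly inferred.** The article calls the design effect one way to account for clustering, and never writes E_ind + E_clus/DE. This is true, but 600 events counted as 150, followed by a total of effective events, has no other natural reading.
- **The 90% is stated for the individually randomised design.** A reader might infer that the article claims verified 90% power for the blend. It does not, and its Conclusion says that the blended analyses would benefit from further investigation. It does, however, carry the 150-event target over to the mixture.
- **Cluster randomization is described as less likely to be selected.** This makes a mixture less probable but does not remove the loss, which is steep at small shares: 5% already cuts 150 to 113 at DE = 4.
- **Stratified models and meta-analysis are mentioned.** Stratification frees the baseline hazards but leaves each event with equal weight. Meta-analysis is offered only as an alternative. The equivalence sentence, as a general statement, is not an error. A reader might take it as reassurance that pooling and inverse-variance weighting agree here, but it refers to model-based variances and does not carry over to robust variances under clustering.
- **The weights are also a choice of estimand.** This stands. The article itself says that individual randomization targets the direct effect and cluster randomization the total effect, so re-weighting changes what the blended VE means.

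**Conclusion.** The concern holds: following both stated rules gives a true mixture less information than its target claims. At the article's DE of 4, 150 additive effective events are worth between 96 and just under 150, depending on the mix. With 4.95 the floor is about 84. Power falls from about 90% to about 75% at 96 events and 80% at 110.

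A reader might infer a fixed loss for every blended trial, such as 86 to 130 events. The article does not support that. Those figures correspond to an assumed cluster share of 25% to 75%, and the low end needs DE = 4.95 rather than the stated 4. The loss vanishes at either extreme. The gap between 4 and 4.95 is a separate matter.

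The sandwich variance keeps the type I error of each test, so the harm is to power, precision and information timing. Severity is should-fix, because it arises only if a mixture occurs. The result rests on reading the effective-event total as additive, on one common design effect for the cluster data, and on independence between designs, which the article assumes.

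**What to change.** Choose one of two routes and write it into the blending and sample-size sections.

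(a) **Change the weights.** Estimate the log hazard ratio within each design, with a robust variance for cluster-randomised data, and combine by inverse robust variance. The additive count is then the right trigger. The cost is more than wording. The weights depend on estimated variances, and the blended VE moves towards the individually randomised (direct) effect. In the 50:50 case at DE = 4, the cluster weight drops from 300/375 = 80% to 50%. The text should say so.

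(b) **Keep the pooled model and its weights.** Time the looks at 50, 100 and 150 on its actual information, either (E_ind + E_clus)²/(E_ind + DE × E_clus) or the inverse robust variance. The cost is a longer trial: at DE = 4 the additive count must reach about 233, 204 or 174 for cluster shares of 25%, 50% or 75% (150²/I). Alternatively, keep 150 additive effective events and restate the mixture's power over a range of cluster shares.

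Under either route, add one sentence saying that the equivalence with inverse-variance meta-analysis refers to model-based variances and does not carry over to robust variances under clustering.

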## Conclusion

We have described a vaccine trial design for identifying an efficacious MARV vaccine as rapidly and efficiently as possible. This event-driven, platform trial design takes into account the potential sporadic spread of MARV over a wide range in Sub-Saharan Africa. The design incorporates elements of the successful ring vaccination trial structure that was employed to find an efficacious vaccine for Ebola in 2015 in Guinea.^23,24^ In that trial, a vesicular stomatitis virus-based vaccine expressing a surface glycoprotein of Zaire Ebolavirus was found to be safe and highly efficacious at the interim analysis with 90 clusters (i.e. rings), 48 with immediate vaccination and 42 with delayed vaccination, comprising a total of 7651 participants. For MARV, there have been 13 outbreaks since 1967.^
25
^ Most of these outbreaks have been small, with fewer than 30 cases. However, the 2005 outbreak in Angola had 374 cases, and the 1998–2000 outbreak in the Democratic Republic of the Congo totalled 154 cases. Both of these outbreaks would have passed the threshold of 150 cases needed to carry out a final analysis with the vaccine trial design described here. The timing and size of future MARV outbreaks remains uncertain, but as mentioned above, there is evidence of increased circulation of MARV in Central and Western Africa. In addition, there are a host of other potential filovirus and other infectious disease threats, with epidemic and pandemic potential, that could emerge without warning.^
9
^ The vaccine trial design described here could be quickly implemented should any of these threats emerge, although it could take several outbreaks to accumulate enough evidence to assess the efficacy of the vaccines deployed in the trials.

Currently, the World Health Organization COVID-19 Solidarity Vaccines trial^
7
^ is being deployed for the assessment of COVID-19 vaccines in multiple sites within multiple countries. This individually randomized, placebo-control trial fits roughly into category 1.a., in Figure 1. One important selection criterion for the Solidarity Vaccines trial populations has been to have an approximate 0.5%–1% COVID-19 cumulative incidence in the placebo arm over the average duration of follow-up. Other important selection criteria for sites include the ability to conduct the trial, including achieving targeted levels of enrolment and retention, and the need for more COVID-19 vaccines in the country. We propose building on the World Health Organization Solidarity trial design by adding the ability to assess the VE from transmission clusters and individual populations, to accelerate the case counts to meet the proposed endpoint totals. We allow for combining information across trial designs that involve both individual and cluster randomization. The goal would be to achieve an average 1% cumulative case incidence across the clusters. Because cluster-randomized designs require a substantially larger sample size than individually randomized trials, and because it is difficult to ensure comparability of baseline risk unless the number of clusters is very large, this design is less likely to be selected. The evaluation of performance characteristics for the blended analyses of individual and cluster-randomized would benefit from further investigation. Finally, like the World Health Organization Solidarity trial, we propose trial coordination of the different designs into a platform trial with a single steering committee and data monitoring committee. This proposed vaccine trial design can be implemented when MARV outbreaks occur, or for other emerging pathogens of high importance.
